### Laboratory measurement of drug concentrations and sample handling

After blood sample collection, blood samples will immediately be placed in a dark cooler box and transported to the laboratory within 30 minutes of collection, after which samples will be centrifuged, aliquoted, batched, and frozen at -80ªC until quantification of drug concentrations is done. Quantification of the drug concentrations will be performed using pre-established validated liquid chromatography mass spectrometry (LC-MS) methods and high-performance liquid chromatography with ultraviolet detection (HPLC-UV).

### Safety assessment

A creatinine level will be measured in patients who undergo intensive pharmacokinetic blood draws, acutely ill in-patients and out-patients without a recent measurement. All other safety testing will be performed according to standard of care. Participants who are found to be pregnant during follow-up will not be excluded, however, pharmacokinetic data will be censored at that point.

Adverse event (AE) assessment and reporting will be conducted for participants undergoing dose adjustments for tuberculosis treatment. All observed or volunteered AEs, regardless of suspected causal relationship, will be reported. Adequate information will be obtained to evaluate the causality and severity of the AE using the Naranjo score and Division of AIDS (DAIDS) table respectively. Following adverse events, follow-up will be conducted until the event or its sequelae resolve or stabilize. Participants who suffer harm will be managed by the study which has provided trial insurance for those receiving dose adjustment.

### Statistical analysis

**
*Analysis of data on antimicrobial drugs: sparse pharmacokinetic data*
**

Sparse pharmacokinetic data for antimicrobials will be analysed as medians with standard deviations. We assess for the effect of covariates like age, sex, body-mass index, CD4 cell counts on drug concentrations

**
*Analysis of data on antimicrobial drugs: intensive pharmacokinetic data*
**

Non-linear mixed-effects models will be used to calculate the pharmacokinetic parameters of the drugs and this will include the maximum plasma concentration (Cmax), time to maximum plasma concentration (Tmax), and area under the plasma concentration-time curve (AUC). We will also explore the effects of covariates like age, sex, concomitant medications, and body-mass index on the pharmacokinetic parameters.

**
*Pharmacodynamic parameters*
**

We will use pharmacokinetic and pharmacodynamic models to assess the effect of the pharmacokinetic parameters on clinical response. For sparse pharmacokinetic data, we will use drug concentrations as a covariate in the linear regression models predicting clinical response. Clinical response will be defined as either clinical cure (resolution of symptoms) or clinical failure (lack of improvement in signs and symptoms of infection or recurrence of signs/symptoms of infection after initial improvement or death considered at least possibly due to the infection.

**
*Analysis of data on anti-tuberculosis drugs*
**

For participants on anti-tuberculosis drugs, we will evaluate whether dose adjustment leads to the achievement of therapeutic targets.

As an exploratory objective, using Kaplan Meier survival analysis, time to sputum culture negativity will be compared for those who received dose adjustment and those who did not receive dose adjustment within this study. We will also utilize the SOUTH dataset where drug concentrations of rifampicin and isoniazid were measured (without dose adjustment), where 78% and 84% of participants had rifampicin and isoniazid concentrations below the therapeutic targets respectively.

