**Primary endpoints**

Pharmacokinetic parameters

Trough concentrations (Ctrough) for amoxicillin, ciprofloxacin, azithromycin and ceftriaxone

Pharmacodynamic parameters

Clinical response to antibiotics through the time of treatment will be assessed. Clinical response is either clinical cure (resolution of symptoms) or clinical failure (lack of improvement in signs and symptoms of infection OR recurrence of signs/symptoms of infection after initial improvement.

**
*On TB treatment*
**

Pharmacokinetic parameters

Maximum concentrations (Cmax) and area under the concentration-time curve (AUC) defined as the total exposure for rifampicin, isoniazid

Pharmacodynamic parameters

1. Clinical response will be assessed according to the World Health Organization definitions of cure, completed and treatment failure, which will be extracted from the clinic database.2. Occurrence of adverse drug reactions

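### Antibiotic clinical response is cure or failure, but the plan names linear regression for it and defines failure in two ways, with death in only one of them

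*Protocol article*

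**What the plan says.** All references are to the protocol article.

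- **Endpoint.** Study outcomes places clinical response to antibiotics under Primary endpoints: "Clinical response is either clinical cure (resolution of symptoms) or clinical failure". Failure there means "lack of improvement in signs and symptoms of infection OR recurrence of signs/symptoms of infection after initial improvement", and the list ends at that point.
- **Analysis.** Statistical analysis, Pharmacodynamic parameters, uses the same two categories: "Clinical response will be defined as either clinical cure (resolution of symptoms) or clinical failure". It gives the same two routes to failure and adds a third: "or death considered at least possibly due to the infection".
- **Model.** The same paragraph first refers to unspecified pharmacokinetic and pharmacodynamic models. For the sparse data it then says: "we will use drug concentrations as a covariate in the linear regression models predicting clinical response".

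No section names a logistic or other binary-outcome model, and none reconciles the two definitions of failure.

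**The concern.** There are two separate defects, both in what the article states and not in what it leaves out.

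First, the named model does not match the outcome. Linear regression treats cure (1) or failure (0) as a continuous quantity with the same variance at every concentration. The fitted line is unbounded, so it can predict cure probabilities above 1 or below 0. One study objective is a pharmacokinetic-pharmacodynamic model for use during drug monitoring, so an estimate that cannot be read as a probability is of limited use.

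Second, one listed primary endpoint has two definitions. Whether some deaths count as failures depends on the section followed. If that is settled after outcomes are known, it becomes a post hoc choice on a primary endpoint. Enrolment began in September 2024, so the wording should be settled before the outcome data are examined.

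**Working it through.** The article gives no figure for this analysis, so there is none to reproduce. The check compares the text and adds an illustration under stated assumptions.

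**1. Constant variance.** A two-value outcome with cure probability p has variance p(1 − p). At p = 0.80 this is 0.80 × 0.20 = 0.16; at p = 0.95 it is 0.95 × 0.05 = 0.0475. If concentration affects cure, the variance must change along the concentration axis.

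**2. Fitted values outside 0 to 1.** Inputs:
- n = 42: 50 per oral antibiotic less the upper 15% attrition, 50 × 0.85 = 42.5 (Sample size).
- Cure 80%: the only success rate in the article, a background figure for pneumonia (Introduction). It is used as an assumption.
- Odds ratio 2.7 per e-fold of concentration: an assumption, not in the article.
- CV of concentration: 30% is the exposure CV assumed for oral drugs (Sample size). The covariate here is a measured concentration, largely troughs, whose CV is not given, so 60% and 100% are also shown.

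Concentrations were drawn as lognormal, cure was generated from logit(p) = a + ln(2.7) × ln(concentration) with a set to give 80% cure, and ordinary least squares was fitted to raw concentration.

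| CV | Fits with at least one fitted value outside 0–1 |
|---|---|
| 30% | about 34% |
| 60% | about 63% |
| 100% | about 83% |

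The average share of fitted values outside the range is much smaller: about 2% at CV 30% and 4% at CV 60%. Fitting log concentration lowers the share of affected fits to about 26% and 47% respectively. With no true effect, about 18–23% of fits are affected and the test rejects in about 5% of data sets.

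**3. Number of failures.** At an assumed 20% failure rate, 0.20 × 40 = 8 and 0.20 × 50 = 10 failures per oral antibiotic. For ceftriaxone, reading the 25 in Sample size as the number on that drug, 0.20 × 25 = 5, or 0.20 × 21 = 4.2 after 15% loss.

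**4. The two definitions side by side.**

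| Course | Primary endpoints | Statistical analysis |
|---|---|---|
| Death with infection never improved | Failure (lack of improvement) | Failure |
| Death after recurrence | Failure (recurrence) | Failure |
| Death after initial improvement, no recurrence, possibly infection-related | Not classified | Failure |
| Death after initial improvement, no recurrence, judged unrelated | Not classified | Not classified |

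The sections conflict on the third row. The fourth is open in both. With about 4 to 5 ceftriaxone failures expected, one reclassified death changes the count by about 1/5 to 1/4.2, or 20% to 24%.

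**The case against.** The strongest reply is that little depends on this. The linear-regression sentence covers only the sparse data, other pharmacodynamic models are named alongside it, and nothing makes the concentration-response regression itself a primary analysis. Test size is close to nominal, few individual fitted values are out of range, and a linear probability model with robust standard errors can be defended.

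Part of this stands. The association test survives, and it would be wrong to call the regression the primary analysis: clinical response is a listed primary endpoint, but its regression on concentration is not so designated. However, the article states no linear probability model and no robust errors. The sparse data are not marginal either. Intensive sampling is planned for 20 participants per oral drug against 50 enrolled, and ceftriaxone has two draws per participant.

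Three stronger readings are tempting but unsupported:

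- **That anyone who dies is neither cured nor failed under the endpoint section.** A death with unimproved or recurrent infection already fits its wording for failure.
- **That the same fault affects the TB endpoint.** TB response defers to the "World Health Organization definitions of cure, completed and treatment failure". That source is not shown, so how it treats death or loss cannot be judged here. The TB analyses described are target attainment and time to culture negativity, with no regression of TB clinical response.
- **That most linear fits will give impossible probabilities.** The 63% rests on an assumed CV of 60%. At the article's own exposure CVs of 25–30% the share is about 34% or less.

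**Conclusion.** The point holds for the antibiotic clinical response endpoint. The outcome is binary in both sections, the model named for the sparse data is linear, and the two sections disagree on whether a possibly infection-related death after initial improvement without recurrence is a failure.

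The model defect is moderate. It harms effect estimates and predictions, not the type I error rate. The 34% and 63% depend on the assumed n, cure rate, odds ratio and CV, and illustrate the problem without forecasting this study. The definition defect needs no assumption, since it can be read directly from the text. Its numerical effect cannot be computed because the article gives no death rate. It matters most for the acutely ill ceftriaxone in-patients, where few failures are expected and a death is most plausible.

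**What to change.** 1. In Statistical analysis, Pharmacodynamic parameters, replace linear regression for the sparse data with logistic regression of cure versus failure on drug concentration. Use a penalised fit (for example Firth), because only about 8 to 10 failures per oral antibiotic are expected at the assumed 20% failure rate. Report odds ratios with 95% confidence intervals.
2. Use one definition of failure in both sections by carrying the death clause of Statistical analysis into Primary endpoints.
3. State in both places how other deaths, those judged unrelated to the infection, are classified.

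The cost is a change of wording and of model, with no new data or visits. The downside is that odds ratios from so few failures will be imprecise and should be presented as such. The TB endpoint needs no change on this account.

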## Protocol

### Study objectives

1. To determine the concentrations of selected antimicrobial agents in people living with HIV requiring antimicrobial therapy.2. To assess the utility of therapeutic drug monitoring in achieving therapeutic targets for people living with HIV receiving rifampicin and isoniazid for treatment of tuberculosis.3. To develop and validate a population pharmacokinetic-pharmacodynamic model for use during therapeutic drug monitoring for selected antibiotics used among PLWH

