### Participants on anti-tuberculosis treatment

The current tuberculosis (TB) treatment involves fixed dose combinations based on weight bands, including an intensive phase of rifampicin, isoniazid, ethambutol, and pyrazinamide (RHEZ) for 2 months, followed by a continuation phase of isoniazid and rifampicin (HR) for 4 months. Dosing is determined by weight bands, with 3, 4, or 5 tablets of RHZE or HR depending on weight (<55, 55–69, ≥70 respectively). Each tablet contains 150 mg of rifampicin and 75 mg of isoniazid for both combinations. Fixed dose combinations in the intensive phase include concomitant pyrazinamide and ethambutol.

Serum rifampicin and isoniazid concentrations (C2hr, C4hr, C6hr) will be measured in participants when fasting, and following directly observed therapy, after two weeks of treatment (First TDM). Results of blood concentrations will be received within 24–48 hours and assessed to determine if the C
_max_ and AUC is within the therapeutic targets. Sub-therapeutic C
_max_ concentrations are considered less than 8mg/L and 3mg/L for rifampicin and isoniazid, respectively. AUCs for rifampicin and Isoniazid will also be considered and compared with existing published therapeutic ranges
^
22
^. Participants found to have subtherapeutic drug exposures will have dose escalation and be asked to take one additional pill of the drug that did not achieve therapeutic target concentrations (rifampicin, isoniazid or both) (
Table 3). A second blood draw for measurement of drug concentrations will be performed after another two weeks (Second TDM) and dose adjustment performed again based on the guidance in
Table 3, if concentrations are still below the target. (
Figure 1)

**Table 3. T3:** Dose adjustment table for isoniazid and rifampicin in patients with HIV.

Weight band	Normal drug levels	Sub-target INH <3mg/dl Normal RIF	Normal INH Sub-target RIF <8mg/dl	Sub-target INH <3mg/dl and Sub-target RIF <8mg/dl
<55kg	Continue INH 225 mg and RIF 450 mg (3 FDCs)	Give an additional INH tablet equivalent to: INH 300 mg	Give an additional rifampicin tablet equivalent to 600 mg dose	Give additional rifampicin and isoniazid tablets or FDCs equivalent to 300 mg INH and 600 mg rifampicin

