**Figure 1. f1:**
[figure not shown]
Therapeutic drug monitoring procedure with dose adjustment for participants on TB drugs.

If the participant is still not achieving the therapeutic target concentrations after the second C
_max_, another 1hr and 6hr blood draw will be conducted to assess for the presence of fast or delayed absorption. An additional dose adjustment with 1 additional tablet of the respective drug may be prescribed for these patients at the discretion of the study team and with consideration of observed side effects, treatment response, and concentrations attained. Those who attain therapeutic drug concentrations during TDM will revert to the previous dose. The final doses provided will be recorded for all participants.

**
*Sputum analysis*
**

For participants with tuberculosis, sputum cultures will be conducted at the Makerere University Microbacteriology laboratory. Cultures using Mycobacterium Growth Indicator tube (MGIT) and Lowenstein-Jensen (LJ) agar will be conducted within 7 days of enrolment and will be conducted every two weeks for the first eight weeks of TB treatment (intensive phase).

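### Target attainment after dose escalation will partly reflect regression to the mean, because Objective 2 has no reference for what would happen at an unchanged dose

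*Protocol article*

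**What the plan says.** Objective 2 of the protocol article is "To assess the utility of therapeutic drug monitoring in achieving therapeutic targets for people living with HIV receiving rifampicin and isoniazid" for treatment of tuberculosis. The section on participants on anti-tuberculosis treatment describes one sampling day at week 2, with draws at 2, 4 and 6 hours. For sub-therapeutic Cmax it reads: "concentrations are considered less than 8mg/L and 3mg/L for rifampicin and isoniazid, respectively". AUC is also considered. The consequence is fixed: "Participants found to have subtherapeutic drug exposures will have dose escalation". Concentrations are measured again two weeks later. The text under Figure 1 adds that those still below target have further draws to "assess for the presence of fast or delayed absorption" and may be adjusted again.

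Under Statistical analysis, the whole plan for this objective is that "we will evaluate whether dose adjustment leads to the achievement of therapeutic targets". A comparison of adjusted with non-adjusted participants appears only for time to culture negativity, which is labelled exploratory. The external SOUTH dataset, which had no dose adjustment, is mentioned in that same paragraph.

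**The concern.** Participants are selected for a low value, all of those selected are treated, and the same variable is then re-measured. This is the standard setting for regression to the mean. Levels vary within a person between occasions: the protocol provides for variable absorption, and its Discussion concedes that adherence between sampling days cannot be ascertained. Those chosen for a low first result will therefore be higher on average at the second, even at an unchanged dose. The further sampling of those still low gives another chance of spontaneous crossing.

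No low participant stays on the unchanged dose, and nothing is re-measured before escalation. An attainment rate or a paired before-after change therefore cannot, on its own, separate the dose effect from this drift. What is at stake is the answer to Objective 2: the benefit of monitoring-guided dosing on target attainment would be overstated.

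**Working it through.** **Inputs from the protocol.** Share below target without dose adjustment: 78% rifampicin, 84% isoniazid (Statistical analysis, SOUTH). CV of exposure for the tuberculosis drugs: 25%; number of participants: 25; withdrawal: 15% (Sample size). Dose ratios from Table 3, reading its figures as new total doses: 600/450 = 1.33, 750/600 = 1.25, 900/750 = 1.20; isoniazid gives the same ratios (300/225, 375/300, 450/375).

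**Assumptions.** Log-normal concentrations, dose-proportional exposure, and an occasion-to-occasion correlation r of 0.3 to 0.9. The protocol gives no r.

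**The plan's own figure.** The protocol states no expected attainment, so there is none to reproduce. The 25 can be neither confirmed nor refuted, because alpha, power and group structure are not given. With a 30% effect, CV 25%, two-sided 5% and 80% power assumed: 2 × (1.96 + 0.84)² × 0.25² / 0.30² ≈ 10.9, so 11 per group, 22 in total, and 22/0.85 ≈ 26. Other choices of scale and power give 19 to 45. The result below uses the 25 only to turn percentages into counts.

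**Step 1: crossing with no dose change.** The standardised cut-off is c = Φ⁻¹(0.78) = 0.772 for rifampicin and Φ⁻¹(0.84) = 0.994 for isoniazid. Then P(second ≥ c | first < c) = 1 − Φ₂(c, c; r)/Φ(c), which does not depend on the CV.

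| r | Rifampicin | Isoniazid |
|---|---|---|
| 0.3 | 1 − 0.6372/0.78 = 18.3% | 1 − 0.7261/0.84 = 13.6% |
| 0.5 | 1 − 0.6600/0.78 = 15.4% | 1 − 0.7433/0.84 = 11.5% |
| 0.7 | 1 − 0.6876/0.78 = 11.8% | 1 − 0.7649/0.84 = 8.9% |
| 0.9 | 1 − 0.7270/0.78 = 6.8% | 1 − 0.7966/0.84 = 5.2% |

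It is zero only at r = 1. Of 25 participants, 19.5 would be low on rifampicin and 21 on isoniazid. At r = 0.5 about 3.0 and 2.4 of them cross unaided; at r = 0.9, 1.3 and 1.1.

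**Step 2: share of apparent successes.** On the log scale σ = √ln(1 + 0.25²) = 0.246. With a dose ratio k, attainment among low participants is 1 − Φ₂(c, c − ln k/σ; r)/Φ(c). Attainment for k = 1.20 / 1.25 / 1.33, with the Step 1 rate as a share of it:

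| r | Rifampicin attainment | Share | Isoniazid attainment | Share |
|---|---|---|---|---|
| 0.3 | 44.1 / 50.9 / 61.4% | 41 / 36 / 30% | 36.5 / 43.0 / 53.6% | 37 / 32 / 25% |
| 0.5 | 41.0 / 47.9 / 58.9% | 38 / 32 / 26% | 34.0 / 40.6 / 51.5% | 34 / 28 / 22% |
| 0.9 | 34.7 / 42.9 / 55.7% | 20 / 16 / 12% | 28.9 / 36.4 / 48.7% | 18 / 14 / 11% |

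The range is roughly 11-41%. At an assumed CV of 50% and k = 1.25, the share is 42-54% for r = 0.3 to 0.7.

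**Step 3: paired concentrations.** The spontaneous log rise among low participants is (1 − r) × σ × φ(c)/Φ(c). For rifampicin at r = 0.5 this is 0.5 × 0.246 × 0.380 = 0.047. A naive paired log change therefore shows 0.223 + 0.047 = 0.27 when the true effect of a ×1.25 step is ln 1.25 = 0.22. Simulation with 25 participants and r = 0.5 agrees: the naive change averages about 0.27, and a joint mixed model of both occasions recovers about 0.22.

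**The case against.** The strongest reply is that the plan gives one sentence and no estimator, and a condensed article may leave that to an analysis plan. The Abstract foresees non-linear mixed-effects models, and Objective 3 is a population model for use during monitoring; such a model could separate within-person variation. This stands in part: the protocol does not commit to a naive comparison. But the selection rule, the escalation of all low participants and the causal wording are fixed here. The section on the tuberculosis drugs names no model, and a Week 4 draw in non-escalated participants must be secured in advance.

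A reader might infer that attainment will be judged only in escalated participants. The text refers to participants on anti-tuberculosis drugs generally, and Table 1 lists a Week 4 draw where applicable, so that restriction is not stated. Nor is selection on a single value: it is one occasion with three samples.

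SOUTH could be called the control. As described, it supplies proportions for all participants, not for a re-measured low subgroup, and repeat levels are not mentioned.

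A reader might also infer that up to half of the successes are spontaneous, or that a harmful escalation policy could look useful. The first needs a CV near 50%, not the protocol's 25%. The second does not follow: harm is followed separately through the adverse-event grading under Safety assessment and the triggers under Data Monitoring Committee, and drift in concentrations does not hide toxicity.

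**Conclusion.** The point holds as a bias of known direction and moderate size. On the stated assumptions, 7-18% of low rifampicin and 5-14% of low isoniazid participants would reach target with no dose change. That is roughly 11-41% of apparent successes at the protocol's CV of 25%, and more if the true CV is larger. At CV 25% the dose step still accounts for most of the gain. The main uncertainty is the occasion-to-occasion correlation, which the protocol does not give; it changes the size of the bias but not its direction. The analysis should be changed, because this is a stated study objective and the change is cheap.

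**What to change.** 1. Take the Week 4 draw already in Table 1 in every tuberculosis participant, escalated or not, for both drugs.
2. Analyse log concentrations from both occasions jointly, in a mixed or population pharmacokinetic model with inter-occasion variability and the actual dose of each drug as a time-varying covariate.
3. Report observed attainment beside the model-expected attainment at the unchanged dose.
4. State that the model assumes no time trend between the visits. Pairs without a dose change will be few, about 25 × 0.22 = 5.5 for rifampicin and 25 × 0.16 = 4 for isoniazid before withdrawal, and they lie mostly above the cut-off, so the data can hardly test that assumption.
5. If this is not done, replace the causal wording with a descriptive statement, such as *proportion attaining target after adjustment*.

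The cost is a few extra Week 4 draws, revised analysis wording, and a stated effect that is slightly less favourable and less precise. No dose or clinical rule is changed.

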## Introduction

Antimicrobial resistance (AMR) is on the rise and is predicted to become the leading cause of after cancer by 2050, with Africa bearing a significant proportion of this burden
^
1
^. In 2019, an estimated 1.27 million deaths were attributed to antimicrobial-resistant infections, and most of these infections were bacterial
^
1
^.

Optimal dosing of antimicrobial agents is essential to achieve therapeutic concentration, maximize efficacy, and minimize both resistance and toxicity. Conversely, suboptimal drug levels may cause treatment failure, AMR, and mortality, while excessive exposures may increase toxicity and affect adherence
^
2
^. In sub-Saharan Africa, overlapping diseases lead to multi-morbidity with altered physiologic states, like those seen in infections or inflammation, and obesity
^
3
^. These require co-treatment with multiple regimens which may result in drug-drug interactions (DDI) that are often inadequately characterized. The SOUTH study found sub-therapeutic levels of rifampicin and isoniazid amongst TB-HIV coinfected patients, which were associated with delayed sputum conversion
^
4
^ and, as seen in other studies, TB relapse
^
5
^. Such findings have prompted trials of higher anti-TB doses to improve outcomes and prevent resistance
^
6–
8
^. Similarly, suboptimal antibiotic exposure has been associated with poor treatment outcomes
^
9
^ and development of resistance
^
10
^.

People living with HIV (PLWH) are at an increased risk of AMR across a range of pathogens and drug classes
^
11
^. Antibiotics are frequently prescribed in PLWH to manage co-morbidities like other sexually transmitted- and urinary tract infections as well as respiratory tract infection. Prescription rates of these vary widely, ranging from about 40% in Nigeria to as high as 85% on Tanzania
^
12
^. While this data was not available for Uganda, a recent general survey showed widespread antibiotic use across hospitals
^
13
^. Outcome data for common infections indicate an 80% treatment success rate for pneumonia, a major cause of mortality amongst especially children in Uganda. However, resistance to commonly used antibiotics is on the rise in Uganda, with reported rates exceeding 70% for ceftriaxone and ampicillin, and about 43% for ciprofloxacin
^
14

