### Sample size

We conducted a priori stochastic simulation and estimation to determine the appropriate sample size for our study. Assuming a 30% coefficient of variation (%CV) in drug exposure, we estimated that enrolling 40 participants per antibiotic would provide sufficient power to detect a 30% effect of HIV co-treatment on antibiotic exposure. In alignment with the ICH E9 guidelines on statistical principles for clinical trials and considering an anticipated 10–15% attrition rate due to study withdrawal and loss to follow-up, we increased the sample size by 10 participants per antibiotic. This adjustment results in a total of 50 participants per antibiotic, or 200 participants overall.

For intravenous antibiotics (ceftriaxone) and anti-TB drugs (rifampicin and isoniazid), we assumed a lower %CV of 25% in drug exposure. Based on this assumption and accounting for an anticipated 15% withdrawal rate, we estimate that a sample size of 25 participants will be sufficient to maintain the power needed to detect possible significant changes in drug exposure due to concomitant antiretroviral therapy.

Therefore, the total sample size for this study is 200 participants.

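### The exploratory culture comparison sets dose-adjusted participants against those at target on both drugs, so it is confounded by indication and biased against showing a benefit of adjustment

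*Protocol article*

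**What the plan says.** In the Protocol article, the Statistical analysis section on anti-tuberculosis drugs first asks whether dose adjustment leads to target attainment. It then adds a second analysis, introduced with "As an exploratory objective, using Kaplan Meier survival analysis", in which "time to sputum culture negativity will be compared for those who received dose adjustment and those who did not receive dose adjustment". This contrast is restricted to the present study. The next sentence says that the SOUTH dataset, in which no doses were adjusted, will also be used, and describes it as one "where 78% and 84% of participants had rifampicin and isoniazid concentrations below the therapeutic targets respectively". It does not say what role SOUTH plays.

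Three other places bear on this:

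- Participants on anti-tuberculosis treatment: "Participants found to have subtherapeutic drug exposures will have dose escalation". Table 3 gives an increase in every below-target column and leaves the dose unchanged only when both drugs are normal. The first measurement comes after two weeks of treatment. Under Sputum analysis, cultures start within 7 days of enrolment and run two-weekly to week 8.
- Introduction: SOUTH found "sub-therapeutic levels of rifampicin and isoniazid amongst TB-HIV coinfected patients, which were associated with delayed sputum conversion".
- Sample size: for ceftriaxone and the anti-TB drugs, "we estimate that a sample size of 25 participants will be sufficient", after "accounting for an anticipated 15% withdrawal rate".

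**The concern.** A comparison of adjusted with unadjusted participants estimates the effect of adjustment only if the two groups would otherwise have had similar outcomes. Here the rule that assigns adjustment is the drug level itself, and the protocol cites evidence that low levels go with slower conversion. The groups therefore differ at the outset on the very factor that adjustment is meant to correct.

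The relevant counterfactual is a participant with low levels whose dose was left alone. Nobody in this study fits that description if the protocol is followed. If adjustment works, the adjusted group catches up at best. If it does nothing, the adjusted group looks worse. Both results would look like no benefit or harm.

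What is at stake is the reading of the only culture-based comparison of dose adjustment that the protocol spells out. Objective 2 is the utility of drug monitoring, and the Discussion hopes to guide dosing practice.

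**Working it through.** **The plan's own numbers.** Three oral drugs at 50 each, plus 25 on ceftriaxone and 25 on TB treatment, give 3 × 50 + 25 + 25 = 200, the stated total. For withdrawal, 21 / 0.85 = 24.7, rounded up to 25, so 25 enrolled corresponds to about 21 evaluable (25 × 0.85 = 21.25). No effect size, error rate or power is stated for the culture comparison, so there is no further figure to reproduce.

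**Who is unadjusted.** Adjustment follows if either drug is below target, so the unadjusted are those at target on both. With 78% below target for rifampicin and 84% for isoniazid:

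- Upper bound on the share: min(1 − 0.78, 1 − 0.84) = 0.16. Expected number 25 × 0.16 = 4.0, or 21.25 × 0.16 = 3.4 evaluable.
- If the two drugs are independent: 0.22 × 0.16 = 0.0352. Expected number 25 × 0.0352 = 0.9. The chance that nobody is unadjusted is then about 41%.
- Lower bound: max(0, 1 − 0.78 − 0.84) = 0.

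These are expected values. At the 16% ceiling, the realised count, Binomial(25, 0.16), has a 95% range of 1 to 8. If the TB cohort were 50 instead of 25, the expected numbers would be 8.0 at the ceiling and 1.8 under independence.

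**Precision (illustrative).** The protocol gives no conversion rate. Assume 20 to 25 conversions, the 16% split and a two-sided 5% level, with SE(log HR) = 1 / √(d × p × (1 − p)):

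- d = 20: 1 / √(20 × 0.16 × 0.84) = 0.61. The 95% interval spans a factor of exp(1.96 × 0.61) = 3.3 either way.
- d = 25: 1 / √(25 × 0.16 × 0.84) = 0.55. The factor is 2.9.

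With 25 events, power is about 11% for a hazard ratio of 1.5, 25% for 2 and 52% for 3. Fewer conversions would make this worse.

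**Direction of the bias (assumed hazards).** Take a conversion hazard of 0.25 per week at target and half of that, 0.125, below target. By week 2, before any adjustment, 1 − exp(−0.25 × 2) = 39% of the at-target group and 1 − exp(−0.125 × 2) = 22% of the others would have converted. The gap exists before the intervention begins.

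In 4,000 simulated studies of 21 adjusted against 4 unadjusted, with two-weekly cultures to week 8 and a log-rank test:

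| Effect of adjustment from week 2 | Significantly favours adjustment | Significantly against |
|---|---|---|
| Fully restores the hazard | 0.7% | 14% |
| None | 0.1% | 24% |

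A fully effective and a useless adjustment give similar pictures, and both lean adverse.

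**The case against.** Four points can be made for the plan.

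- **The analysis is exploratory.** This stands. The main TB analysis is target attainment, culture conversion is not among the listed TB outcomes, and no test or power is promised. The 80%-power yardstick does not apply, and the precision figures only show how little the curves could tell. A reader might infer that Objective 2 is undermined. The documents do not support that, because target attainment does not depend on this contrast.
- **SOUTH is already named, and described as being without dose adjustment.** This stands in part. The natural reading is that SOUTH would supply an external unadjusted comparison, and an article may leave the matching details to a fuller document. But the role is not stated, and using SOUTH would not repair the within-study contrast, which is fixed in the text.
- **The unadjusted count is not capped at 4.** This stands. Four is a ceiling on the expectation, and it depends on SOUTH rates carrying over.
- **The comparison could still favour adjustment.** A reader might infer that it can never show a benefit. That goes too far: an effect well beyond restoring exposure, or a weaker link between level and conversion than assumed, could still appear. What the documents support is bias against showing a benefit.

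None of this removes the confounding, which follows directly from the escalation rule and the protocol's own statement about low levels.

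**Conclusion.** The concern holds as one of bias and imprecision in an exploratory analysis. As written, the within-study comparison is confounded by indication, and its direction is against dose adjustment. The delay to week 2 adds to this, since cultures begin around enrolment and no landmark is stated. One side is expected to hold at most about 4 of 25 participants, about 1 under independence, and realistically 1 to 8 at the ceiling.

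The direction rests on the protocol's own text: the escalation rule in Table 3 and the cited association of low levels with delayed conversion. The counts rest on two assumptions: that the SOUTH rates apply here, and that 25 is the whole TB cohort, a reading inferred from the total of 200. The hazard-ratio and simulation figures are illustrative. No conversion rate is given, eligibility does not require culture-positive TB, and Table 1 asks for cultures in TB participants only where applicable.

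**What to change.** 1. Present the within-study curves for adjusted and unadjusted participants as descriptive only, and state that no inference about the effect of adjustment will be drawn from them.
2. State the role of SOUTH. The exploratory comparison of dose adjustment is between participants below target at the first measurement here and SOUTH participants below the same cut-offs, whose doses were not adjusted.
3. Start both groups at a common week-2 landmark, among those not yet culture-negative, and adjust for baseline variables held in both datasets.
4. Make this conditional on what SOUTH holds. Its sampling times, culture schedule and size are not in the protocol. If they cannot be matched adequately, say so and keep the analysis descriptive.

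The cost is a change of analysis wording plus data harmonisation, whose extent cannot be judged from the protocol. No visit, sample or dosing rule changes. The landmark drops those who are already culture-negative by week 2, which shrinks an already small group. SOUTH is a historical control, so differences in period and assay will remain and must be stated as limitations.
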